**Fig. 4 Fig4:**
[figure not shown]
The expected number of participants, assuming no dropouts, performing Eriksen Flanker test each year is shown. The grade and birth year are displayed within each column along with the estimated number of participants. Dark grey columns are intervention schools, light grey control schools

#### Stroop test

The Stroop effect is the interference in the reaction time when the name of a colour is printed in a colour not denoted by the name (e.g., “red” printed in blue) [36]. The reaction time is faster when the name of the colour matches the ink colour (congruent) than when the name of the colour does not match the ink colour (incongruent) [37]. A computer-based method was used (Millisecond Software, Seattle, Washington, USA). The descriptions of the key-corresponding colour were in sight on the screen during the test. The pupils were told to respond correctly and quickly, using both hands. Reaction time and accuracy (percentage of possible trials with correct response) is the outcome. Calculation of interference scores (incongruent – congruent) for both reaction time and accuracy will allow for interpretation of the Stroop effect as the difference in speed and accuracy of information processing during the congruent and the incongruent trials [35]. Only certain grade levels, from 4th grade, will attend the Stroop test during the different test years (Fig. 5).

**Fig. 5 Fig5:**
[figure not shown]
The expected number of participants, assuming no dropouts, performing the Stroop test each year is shown. The grade and birth year are displayed within each column along with the estimated number of participants. Dark grey columns are intervention schools, light grey control schools

#### National academic tests

The Norwegian Directorate for Education and Training conducts compulsory national academic tests annually for 5th, 8th and 9th grades pupils. In national level of 5th grade reading, mathematics and English are published with mean values in a 50-point scale, with a SD on 10 points [38].

In the present study results from national tests for 5th grade pupils are collected (Fig. 6). The tests are performed in the fall each year; hence baseline data for the 5th^-2004^ grade pupils in 2015 was collected in fall 2014. As the study progress results from academic test will accumulate for 5th graders. In fall 2019, the last 5th grade (born 2008) will complete their national tests, hence secular trends will be reported. This also permits extraction of individual information about the academic achievement of each pupil at both intervention and control schools. In addition, comparison with national results is possible, however, no measure of one-year intervention effect is possible. [38].

**Fig. 6 Fig6:**

The expected number of pupils, assuming no dropouts, accumulating national academic tests until all pupils passed 5^th^ grade in the study period. Dark grey columns are intervention schools, light grey control schools. The year in each column corresponds to the birth year of the pupils

#### Nutrition

The Norwegian developed and nationally validated dietary questionnaire “Ungkost 2000” concerning nutrition was completed using Questback [39, 40]. “Ungkost 2000” has 18 items including age, gender, PA level, inactivity and parents’ education level, diet and body weight [40]. The diet part of the questionnaire includes items as “ordinary Norwegian diet”, vegetarian/vegan, diabetes, allergies, as well as questions about weight satisfaction and attempts of weight loss. In addition, questions about “your diets role for your health” and if the child consider his/hers diet to be healthy or not are included. The questionnaire also comprises the number of times a week they eat breakfast, lunch, dinner and supper, in addition to how often they eat lunch during weekdays.

An extensive mapping of the amount of milk, orange juice and soft drinks (with and without sugar) is incorporated in the enquiry, as well as a variety of different food products including vegetables, bread, dairy products, fish, fast-food, sweets and vitamins. The enquiry gives a general description of different aspect of children’s nutrition status.

The “Ungkost 2000” is designed for 4^th^ grade pupils, and hence was given to 4th^-2005^ grades in 2015 (Fig. 7). To test the effect of one-year intervention “Ungkost 2000” is repeated for the same pupils in 2016 (5^th-2005^). Each year a new cohort reach 4^th^ grade and complete the test to accumulate data for measuring secular trends.

**Fig. 7 Fig7:**
[figure not shown]
In 2015 the cohort of 4^th^-2005 grades perform the “Ungkost 2000” at baseline, and repeat the test as 5^th^ grade in 2016 as to measure effect of one year intervention. Each year a new cohort reach 4th grade and complete the test. Each cohort is marked with grade and year of birth, in addition expected estimated sample size, assuming no dropouts. Dark grey columns are intervention schools, light grey control schools

#### SDQ, SPPA and friendship nomination

The Strengths and Difficulties Questionnaire (SDQ), The Self-Perception Profile for Adolescents (SPPA) and friendship nomination were given digitally under supervision to pupils in 6^th^ and 7^th^ grades, using Questback. SDQ is a behavioural screening questionnaire for 2–17 year olds inquiring 25 positive and negative attributes [41]. SDQ is divided in five scales, each with five items; emotional symptoms, conduct problems, hyperactivity/inattention, peer relationship problems and pro-social behaviour. The first four items are added together to generate a total difficulties score. SDQ reflects levels of internalizing and externalizing psychopathology within a Norwegian child population [41–44].

SPPA has been widely used in research related to self-concept [20]. The revised version of SPPA was used in the Young in Norway study [45]. The SPPA consist of five items, each rated on a Likert-scale.

Children’s best friend nominations are thought to represent the peers with whom participants affiliate the most strongly [46]. Having close friends during childhood has been linked to improved mental health and resilience in later life [46]. Friendship will be evaluated by use of «best friend» nomination, including the listing of current friends and three best friends [47]. Also, the children will be asked to justify the reason for someone being their best friend. These answers will be organized into different categories as suggested by Thorpe et al. [48].

### Parental questionnaires

Parents annually received the parental version of ILC, which certifies for analyses of cross-sectional data at baseline as well as individual changes in the parental understanding of their child’s QoL across years [27, 28]. Annually an increasing number of tests will be accumulated for each grade as the study progresses, and secular trends for each age group will be established.

Parents also reported their children’s leisure time activity, any illnesses and parent’s education level. The leisure time questionnaires included three alternatives for non-physical activities, including type of activity, times per week and total hours a week. Similar question were given regarding PA, as well as any illness. Parental education level was divided in to elementary school, high school, bachelor degree and master/PhD degree. The parental questionnaire for children’s leisure activity was not validated and serves only as a report of leisure time activity.

#### Analysing tools

All data recorded on paper in the baseline tests were digitalized. The digitalized data from questionnaires were manually controlled for outliers and extreme values to improve validity. Ultimately, all data were unidentified and transferred to SPSS 21 (SPSS inc. Chicago, Illinois, USA) and other statistical software for analyses.

### Analytic possibilities

A longitudinal controlled intervention design like HOPP allows for multiple analyses, from cross-sectional analyse at baseline values, evaluation of effect after one-year intervention, longitudinal effects and secular trends.

#### Main outcome measure

In the present study cardio-metabolic risk factors were calculated by integrating objective measurements of BMI, waist circumference, muscle mass, percentage fat, endurance test, total serum cholesterol, HDL, non-HDL, mCRP and HbA1c. Firstly, all variables were divided into quartiles. Secondly, the results were dictomised as the children in the quartile of highest risk factor were given the score 1, and the children in the other quartiles were scored 0. Thirdly, children categorise with risk factors were assigned to one of 11 risk factor categories, 0–10, depending on their number of risk factors. Fourthly, the probability of children having 0 to 10 risk factors were calculated using the binominal probability formula (*n*! • *p*
^r^ • (1 – *p*)^*n-r*^ / (*r*! • (*n*-*r*)!) [49]. Where *n* is the possible number of risk factors (total of 11), *p* is the probability of having a risk factor (highest risk factor quartile: 0.25) and *r* is the number of risk factors for which the probability is calculated (0–10) [17]. Fifthly, the observed number of children in each group was compared to the expected number by calculating the ratio and plotting with a 95% confidence interval. Finally, a composite cardio-metabolic risk factor profile was calculated using Z-scores by age and gender for selected risk factors. The Z-scores were then summed for each individual regarding the individual risk factors to create the clustered risk score [17].

The occurrence of cardio-metabolic risk factors in the HOPP study was calculated at baseline. In addition, the calculus is to be computed annually to reveal any change in cardio-metabolic risk factors as a result of the intervention.

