**Methods:**

The HOPP study is a 7 years longitudinal large-scale controlled intervention in seven elementary schools (*n* = 1545) with two control schools (*n* = 752); all aged 6–11 years at baseline. The school-based physical activity intervention program includes an increase in physical activity (PA) of 225 min/week as an integrated part of theoretical learning, in addition to the curriculum based 90 min/week of ordinary PA. Primary outcomes include cardio-metabolic risk factors measured as PA level, BMI status, waist circumference, muscle mass, percent fat, endurance test performance, total serum cholesterol, high-density lipoprotein (HDL), non-HDL, micro C-reactive protein (mCRP) and long-term blood sugar (HbA1c). In addition, secondary outcomes include anthropometric growth measures, physical fitness, quality of life (QoL), mental health, executive functions, diet and academic performance.

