### Children’s test

#### Annual measurements for all participants

Measurement of ^1)^ anthropometry, ^2)^ body composition, ^3)^ fitness and ^4)^ PA level, ^5)^ blood pressure, ^6)^ blood samples and ^7)^ The Inventory of Life Quality in children and adolescents (ILC) are to be completed annually for all participants (Table 3). The protocol design allows for baseline analyses, interventional one-year effect analyses, analyses of secular trends and longitudinal effect analyses across the full length of the study. Due to being very time consuming oxygen uptake is restricted to pupils born 2008 (1^st^ grade in 2015).

**Table 3 Tab3:** Based on the various power tests, the following sample size (intervention and controls schools) was calculated, with a beta of 80% and alpha of 5%

Test area	n
Anthropometry	64^b^
Cardio-metabolic risk factors	126^c^
Physical activity level	73^a^
Aerobic capacity	10^a^
General physical capacity	126^c^
Blood tests	34^a^
Quality of life	73^a^
Diet	24^a^
Cognitive ability	85^a^
Academic performance	34^a^

Statistical program: Systat 13, Power Analysis. ^a^One-sample t-test, ^b^Two-sample t-test, ^c^Z-score

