##### 5) Blood pressure

Blood pressure is measured automatically (Model M3 Intellisense HEM-7051-E, Omron Healthcare, Kyoto, Japan) on the upper left arm after being seated on a chair for a few minutes. When fail to detect pressure was apparent, a new test was done immediately. After three unsuccessful tests the cuff was attached to the right arm until a successful test was confirmed.

Whenever the result was outside the expected normal age related range, according to the National Heart, Lung and Blood Institute (NIH), USA, up to three new tests were conducted [25]. With results still outside normal range, a re-test was performed at a later occasion. If the values were persistently outside the normal range the values were reported to the HOPP team physician. The physician then contacted the parents and advised them to contact the child’s general practitioner for further follow-up.

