#### Analyses of effect

Establishing a baseline in 2015 permits a paired comparison of results in 2016, meaning one-year effect analyses of intervention on multiple variables as described in Table 2. The analyses would include test *within-subject* variation as well as *between-subject* variation for both intervention and control schools using basic univariate parametric tests as e.g. t-tests, linear or logistic regression analysis and linear mixed models for repeated measurements. Possible confounding, mediation and/or effect modification will be assessed using stratified and multivariable statistical models and statistical methods for causal inference (e.g. Directed Acyclic Graphs).

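### Blood pressure is measured yearly in every child, but no outcome or between-school comparison is named for it, and the make-up of the main score is unclear

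*Protocol article*

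**What the plan says.** The section on annual measurements for all participants lists seven items (anthropometry, body composition, fitness, physical activity level, blood pressure, blood samples and the ILC quality-of-life inventory), which "are to be completed annually for all participants". Blood pressure has its own procedure: "Blood pressure is measured automatically", followed by rules for failed readings and for repeating readings outside the normal range. The only use described there is referral of persistently abnormal values.

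The Main outcome measure section forms the cardio-metabolic outcome by "integrating objective measurements of BMI, waist circumference, muscle mass, percentage fat, endurance test, total serum cholesterol, HDL, non-HDL, mCRP and HbA1c", which is ten variables. In the binomial step of the same section, n "is the possible number of risk factors (total of 11", while the risk-factor categories run from 0 to 10. The final composite uses "Z-scores by age and gender for selected risk factors", and which factors are selected is not stated.

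The abstract says: "Primary outcomes include cardio-metabolic risk factors measured as PA level, BMI status, waist circumference, muscle mass, percent fat, endurance test performance", and goes on to the blood markers. Neither that list nor the secondary list that follows names blood pressure. The Analyses of effect section speaks of "one-year effect analyses of intervention on multiple variables as described in Table 2".

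**The concern.** The stated main objective is the effect of the programme on cardio-metabolic risk. Blood pressure is collected for all children, and the Discussion itself cites it as an endpoint of earlier school-based trials. Yet no sentence says that it will be compared between intervention and control schools, on what scale, or with what rank. The article does explain why triglycerides and LDL cholesterol are absent (samples were not fasting). It gives no such reason for blood pressure.

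Two things are at stake. First, the ten named components cannot register a change in blood pressure, so that part of the question needs its own analysis. Second, if an analysis is possible but not named, it can be reported or dropped once the results are known.

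**Working it through.** The point rests mainly on setting the sections side by side.

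**1. The seven annual measurements against Table 2**

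| Annual measurement | Row in Table 2 |
|---|---|
| Anthropometry | yes |
| Body composition | yes |
| Fitness | yes (footnote: endurance, handgrip, balance) |
| Physical activity level | yes |
| Blood pressure | no row, no footnote |
| Blood samples | yes (constituents in a footnote) |
| Quality of life (ILC) | yes |

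Six of seven have a row, and blood pressure is the one that does not.

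**2. Outcome lists.** The Main outcome measure section names 10 variables. The abstract's primary list names 11: the same 10 plus physical activity level. The abstract's secondary list has growth measures, fitness, quality of life, mental health, executive functions, diet and academic performance. Blood pressure is named in none of the three.

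**3. Wording that could still cover it.** Directly after the list of seven measurements, the article says that the design allows baseline, one-year effect, secular-trend and longitudinal analyses. Baseline analyses covers cross-sectional analysis of all variables. Analyses of longitudinal effect allows a mixed model for medical and physical results, controlling for baseline. Each of these permits a blood pressure analysis, but none names one.

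**4. The count in the composite.** Ten named variables give eleven categories (0 to 10), so n should be 10. The text sets n = 11. The choice matters for the expected distribution. With p = 0.25, the expected share of children with five or more risk factors is 1 − P(0 to 4):
- n = 10: 1 − (0.0563 + 0.1877 + 0.2816 + 0.2503 + 0.1460) = 0.0781, or 7.8%
- n = 11: 1 − (0.0422 + 0.1549 + 0.2581 + 0.2581 + 0.1721) = 0.1146, or 11.5%

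For the same children, the observed-to-expected ratio in that group under n = 11 is 0.0781 / 0.1146 = 0.68 of its value under n = 10.

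**5. Availability.** The article reports blood samples at baseline in 1344 children and prints 58.4%; 1344 / 2297 = 58.5%. That leaves 2297 − 1344 = 953 children (41.5%) without blood values, for whom blood pressure is nevertheless planned. This supports blood pressure as an outcome in its own right. It does not support putting it in the composite: a score that needs cholesterol, mCRP and HbA1c stays incomplete for those children either way.

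**The case against.** The strongest reply is that this is an editorial gap in a condensed article. Table 2 also omits friendship nomination and the parental ILC, so it is an incomplete summary. Its mention under Analyses of effect is not worded as an exclusive definition. The abstract says that outcomes include the listed items. Which markers belong in a cardio-metabolic score is a choice of construct, and defining one without blood pressure is no contradiction. Changing the score now would alter the main outcome after it had been calculated at baseline.

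Much of this stands. It is why the main score should remain the deciding analysis and why the remedy is small. It does not remove the mismatch between the annual list and Table 2, or the absence of any named comparison.

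A reader might draw four stronger inferences, which the document does not support:
- **That blood pressure is excluded and the trial will conclude without it.** The permissive wording in step 3 and the unlisted factors in the Z-score leave this open.
- **That the missing row in Table 3 is further evidence.** Table 3 lists test areas, not variables. HDL, HbA1c, waist and mCRP have no row of their own either, and its cardio-metabolic row names no components.
- **That blood pressure is the missing eleventh factor.** The abstract reaches eleven with physical activity level, and the categories 0 to 10 are also eleven in number. The text does not decide between these.
- **That the volume of readings measures the harm.** Table 1 with planned exits and no dropout gives 2297 + 2297 + 1872 + 1491 + 1102 + 732 + 351 = 10,142 child-visits. That is a quantity of data, and it shows no bias or loss of power.

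**Conclusion.** The concern holds as a gap in specification. Blood pressure is the one annual all-participant measurement without a Table 2 row, and it is not named in the abstract's outcomes or among the ten components of the main outcome. An analysis is permitted but not named. Separately, the composite cannot be reconstructed from the text: ten named variables stand against n = 11, and the Z-score components are not listed.

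No size of bias follows from the omission. The figure that can be computed concerns the count: the expected share with five or more risk factors is 7.8% for n = 10 and 11.5% for n = 11, under the article's own binomial model with p = 0.25. The conclusion rests on the article alone. A fuller protocol might assign blood pressure a role, but the article's own lists would still need to agree. This is a modest improvement and does not put the main analysis in doubt.

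**What to change.** 1. Add a blood pressure row to Table 2 and name it as a separate outcome with a stated rank.
2. Compare systolic pressure, standardised for age, gender and measured height, between intervention and control schools with the same baseline-adjusted linear mixed model as the other risk factors.
3. State which reading enters the analysis. The procedure repeats only out-of-range readings, so taking the last value for those children alone would pull in the tails of the distribution. This concerns the analysis value only, not the measurement or referral rules.
4. Keep the existing main score as the deciding analysis. List the components of the clustered Z-score, and reconcile the ten named variables with n = 11 and the categories 0 to 10.
5. Report the clustered Z-score with blood pressure added only as a labelled sensitivity analysis. Leave the quartile count as it is, since another factor would require n and the categories to be redefined again.
6. Fix all of this before follow-up data are compared between the two groups of schools.

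The cost is wording, one more outcome and one more sensitivity analysis. The readings are already planned at all schools. If leaving blood pressure out of the score was deliberate, a sentence giving the reason should be added.

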#### Analyses of longitudinal effect

The longitudinal intervention design allows for exploratory analysis of group means over time to discover patterns of systematic variation across groups, as well as among individuals. The design allows for analyses of age and growth effects [50]. As the eldest pupils enrolled at baseline 2015 finish elementary school in 2016, only one year of follow-up is possible. However, an increasing number of years of follow-up are possible with decreasing age at enrolment. This allows for an adjustment of the longevity of being enrolled in the program, and hence measurement of the time-in-the-program effect. Secondly, an annual comparison between the intervention schools and the control schools allows for testing of effect of the intervention. Thirdly, mean values across test time allows for time slopes showing possible effect as an interaction (i.e. effect modification) of intervention and time. A different approach for test across test time may be pre-post analysis of a single follow-up response in conjunction with a baseline measurement [50]. Fourthly, an annual comparison with the upcoming grade within the intervention schools allows for analyses of secular trends.

The longitudinal design in the HOPP study with repeated measures allows for use of a linear mixed regression model using test-year, years of follow-up, intervention versus control school, age and gender as fixed factors for the main outcome of cardio-metabolic risk factors. A similar model may be used for secondary outcomes of academic performance, PA level, cognitive performance, as well as medical and physical results, and simultaneously controlling for baseline values. In addition, the design admits analyses of interaction (i.e. effect modification) between type of intervention group and number of years in intervention.

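### The binomial used for the main outcome takes n = 11 risk factors although only ten are scored, so the expected counts are wrong if computed as written

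*Protocol article*

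**What the plan says.** The Main outcome measure section builds the risk-factor count from "BMI, waist circumference, muscle mass, percentage fat, endurance test, total serum cholesterol, HDL, non-HDL, mCRP and HbA1c", which is ten variables. Each is cut into quartiles, and "the children in the quartile of highest risk factor were given the score 1"; all other children score 0. Children are then "assigned to one of 11 risk factor categories, 0–10, depending on their number of risk factors".

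The expected distribution comes from the binomial formula. Its n "is the possible number of risk factors (total of 11", its p "is the probability of having a risk factor (highest risk factor quartile: 0.25", and r runs from 0 to 10. Observed numbers are divided by expected numbers and the ratios plotted with 95% confidence intervals. The section says that the calculation was done at baseline and will be repeated every year. A composite of summed Z-scores is described as a further step.

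PA level has three different positions. The abstract says "Primary outcomes include cardio-metabolic risk factors measured as PA level, BMI status, waist circumference" and continues to a list of eleven items. The Main outcome measure section does not include PA level. The section on longitudinal effect says "A similar model may be used for secondary outcomes of academic performance, PA level, cognitive performance".

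**The concern.** In this calculation the binomial n is the number of 0/1 items that each child can score. Ten items give counts from 0 to 10, which makes eleven categories. The stated n equals the number of categories, one more than the number of items.

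The expected counts are the yardstick for judging whether risk factors cluster in the same children. With one trial too many, the expected distribution moves towards higher counts. Too few children are expected at zero and too many at five and above. Children without risk factors then look over-represented, and clustering at the high end looks weaker than it is. Because the calculation is annual, the same error would recur each year.

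**Working it through.** **Inputs**, all from the Main outcome measure section: ten listed variables; score 0 or 1; categories 0–10; r = 0–10; stated n = 11; p = 0.25.

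**Can n = 11 be reproduced?** Counting the list gives BMI, waist circumference, muscle mass, percentage fat, endurance test, total cholesterol, HDL, non-HDL, mCRP and HbA1c: ten. The range 0–10 also implies ten. Adding PA level from the abstract gives eleven factors, but the count would then run 0–11, which is twelve categories, against the eleven stated. No reading makes the list, the categories, the range of r and n agree.

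**Formula.** P(r) = C(n,r) · 0.25^r · 0.75^(n−r). Since C(11,r)/C(10,r) = 11/(11−r), the expected count with n = 11 divided by that with n = 10 is

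0.75 × 11/(11−r).

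This equals 1 only at r = 2.75, so no whole-number category escapes. The observed/expected ratio is multiplied by the inverse.

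| r | P(r), n = 11 | P(r), n = 10 | Expected, n = 11 ÷ n = 10 | Effect on observed/expected |
|---|---|---|---|---|
| 0 | 0.0422 | 0.0563 | 0.750 | × 1.33 |
| 1 | 0.1549 | 0.1877 | 0.825 | × 1.21 |
| 2 | 0.2581 | 0.2816 | 0.917 | × 1.09 |
| 3 | 0.2581 | 0.2503 | 1.031 | × 0.97 |
| 4 | 0.1721 | 0.1460 | 1.179 | × 0.85 |
| 5 | 0.0803 | 0.0584 | 1.375 | × 0.73 |
| 6 | 0.0268 | 0.0162 | 1.650 | × 0.61 |
| 7 | 0.0064 | 0.0031 | 2.063 | × 0.48 |

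The factor keeps growing, to 8.25 at r = 10, where almost no children are expected.

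**Summary figures.** The mean count is 11 × 0.25 = 2.75 against 10 × 0.25 = 2.50. P(r ≥ 5) is 0.115 against 0.078. With n = 11 the probabilities over r = 0–10 also fail to sum to 1, because r = 11 is left out. That gap is only 2.4 × 10⁻⁷, but it is another sign that n and the range of r do not belong together.

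**Illustration in counts.** Take N = 1344, the number with baseline blood samples (Blood samples section). This N is an assumption; the number of children with all ten variables is not given, and the ratios above do not depend on it. Expected counts with n = 11 against n = 10 are 56.8 and 75.7 at r = 0, 107.9 and 78.5 at r = 5, and 36.0 and 21.8 at r = 6. Suppose the observed counts matched the ten-factor binomial exactly. Dividing them by the n = 11 expectations, with a half-width of 1.96 × √(N·P·(1−P))/E (P from n = 10, E from n = 11), gives:

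- r = 0: 75.7/56.8 = 1.33 (1.04 to 1.63)
- r = 5: 78.5/107.9 = 0.73 (0.57 to 0.88)
- r = 6: 21.8/36.0 = 0.61 (0.35 to 0.86)

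All three intervals exclude 1 although nothing departs from the ten-factor model. This shows scale only and does not predict the study's data.

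**The case against.** **The counts may be right and only the text wrong.** The article shows no expected counts or ratios, and eleven is the number of categories named shortly before. A reader might infer that the baseline ratios already produced are wrong. The documents support only that they are wrong if computed as written. This objection stands.

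**The effect estimate is not touched.** A reader might infer that the comparison of intervention with control schools is biased. It is not. The multiplier depends only on r, so it cancels in a ratio of two observed/expected values for the same category, between arms or between years. A difference of two such values is rescaled, but its sign does not change. The summed Z-score does not use n, and the linear mixed model has no stated dependence on the binomial. This also stands. It confines the problem to the absolute reading of clustering.

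**Independence cannot hold for these variables anyway.** Non-HDL is total cholesterol minus HDL, and BMI, waist circumference and percentage fat overlap. So n = 10 gives a reference distribution that the data would not be expected to follow even without biological clustering. That limits the interpretation of the ratios, but it is no reason to use the wrong n as well.

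**Perhaps PA level is the eleventh factor.** The abstract's eleven items make this tempting. The Main outcome measure section does not say so, and its list, categories and range of r all point to ten. The status of PA level is therefore a separate inconsistency.

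**Conclusion.** The stated n contradicts the list, the categories and the range of r in its own section. The internal evidence favours n = 10. If n = 11 was used with p = 0.25, observed/expected is inflated by 33% at r = 0 and deflated by 27% at r = 5, 39% at r = 6 and 52% at r = 7. High-end clustering is then understated. These percentages follow from the formula alone and need no assumption about sample size or data; whether they apply depends on which n was actually used.

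Only the absolute clustering reading is affected. A reader might also conclude that the summed Z-score should become the single primary outcome. That does not follow from a wrong n, and nothing in the document requires it.

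The conflicting labels for PA level are real and need reconciling in their own right.

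**What to change.** 1. State n = 10 in the Main outcome measure section, defined as the number of variables scored.
2. Confirm which n was used at baseline. If it was 11, recompute the baseline observed/expected ratios and intervals. If it was 10, only the text changes. Use n = 10 in the annual repeats.
3. Reconcile the status of PA level across the abstract, the Main outcome measure section and the section on longitudinal effect.
4. Do not remove the mismatch by adding PA level to the composite while leaving the rest as it is. Eleven factors would also require a changed list and categories 0–11. The composite would then contain the behaviour that the programme raises directly, so it could improve without any cardio-metabolic change.

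The cost is one number in the text, a check of the baseline calculation with a short re-run if needed, and a decision on how PA level is labelled. No new data are required.
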